**Outcome Assessment**

Primary endpoints:

- Incidence of PTH defined as hemorrhage requiring hemostasis with bipolar electric coagulation, ligature, compression and/or medical treatment with anti-fibrinolytic within the first 24 hours after surgery (early PTH) until 30 days after surgery (late PTH).
- Intraoperative blood loss assessed by a standardized protocol utilizing the gravimetric method. The nurse suctions up 100 ml of NaCl weighed on the scale for precision (Kern & Sohn, PCB 6000-1). The suction canister is also weighed on the scale, as well as the dry gauze. After the surgery the canister of blood including the NaCl is weighed and the dry weights of the canister and gauze including the NaCl are subtracted, this leaves the total blood loss of the operation. It is assumed that 1 gram blood = 1 ml blood.
- Operative time in minutes from the Boyle-Davis gag is placed until it is removed. The operating nurse is responsible for measurements of time.
- Postoperative pain is assessed on an 11-point numeric rating scale ranging from 0 “no pain” to 10 “worst possible pain”. For children, the Wong-Baker Faces rating scale will be used.

Secondary endpoints:

- Patient reported: Unscheduled contacts to the health care system, patient satisfaction, health related quality of life, and patient reported quality of smell and taste via a validated TASTE questionnaire, followed by further investigation should the patient report altered taste at six months.

Variables:

- Patient reported outcome measures (PROMs) of postoperative recovery (return to normal diet, physical activity, and return to work, school, or childcare), compliance to postoperative recommendations.

**Inclusion criteria:** First time tonsillectomy due to; Tonsillar hypertrophy, recurrent tonsillitis (including previous peritonsillar abscess), chronic tonsillitis, systemic complications to tonsillitis, other (mononucleosis), PFAPA (periodic fever, aphthous stomatitis, pharyngitis, cervical adenitis), tonsillar plugs, peritonsillar abscess and signed written consent.

**Exclusion criteria:** Diseases in the hematopoietic system, antithrombotic or anticoagulant drugs in the recovery period, suspicion of or known malignancy, patients, or parents unable to read or speak Danish, patients, or parents unable to use online application for self-evaluation, patients or parents unable to give informed consent, body weight under 16 kilograms.

**Power Considerations:** The sample size calculation is based on data from the Danish Tonsil Database. In a twelve months period, the frequency of PTH causing reoperation with hemostasis was 7.9%. With an expected non-inferiority treatment difference between the IDTS and the cold steel instrument, a significance level of 0.05, a power of 80%, and a non-inferiority limit of 4%, the required sample is 1126 patients. Assuming a drop out frequency of 10% into account, a total of 1250 patients are required. With a non-inferiority limit set to 4%, the present study will be able to detect a clinically relevant change in the frequency of PTH causing reoperation with hemostasis.

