From 2021, ENT departments of the Region of Southern Denmark, and the North Denmark Region have entered the Danish tonsil database collaboration. The database contains pre-, per-, and postoperative information about tonsil surgery, including surgical method and instruments.

Although cold steel tonsillectomy is considered the gold standard surgical technique, several hot techniques including bipolar techniques, diathermy, and coblation have been developed for tonsillectomy^2^. Hitherto, these hot instruments have not proven superior to the gold standard in terms of reducing PTH, and it is recommended, that these hot techniques should be used with caution^2,3,5,8,18,19^. In cold steel tonsillectomy the peritonsillar space is dissected with metal instruments, and bleeding is typically controlled by ligation or electrocautery.

Recently, a new impedance-dependent tissue sealer (IDTS) device (BiZact^TM^) has been approved for all benign indications for tonsillectomy^20^. Preliminary results are promising in terms of a PTH rate of 4.5%, a shortened operative time with a median time of 5.1 minutes (range 1.5-26.5 minutes), and a reduced intraoperative blood loss to 1-10 milliliters^20^. With the IDTS the peritonsillar space is dissected and sealed in one step using adjustable energy from a ValleyLab FT10 Energy Platform (Medtronic) measuring the impedance of the tissue grasped with the instrument securing hemostasis before the surgeon cuts the tissue.

Ideally, if a gold standard technique is to be replaced by a new technique, it is recommended that the decision should be based on scientific studies performed as randomized designs.

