**Method**

*Design*

The project is designed as a Danish randomized controlled multi-center trial of tonsillectomy by conventional cold steel surgical technique versus IDTS. The study is blinded for patients until six months after surgery and the study is assessor blinded.

Randomization is computerized via the tonsil database and utilizes block randomization for each department in a random table of 2000 with equal numbers of group assignments. The randomization is only apparent to the surgeon on the day of the surgery and the day before.

*Course*

All elective and acute patients referred to tonsillectomy, with or without adenoidectomy, on benign indications will be assessed for eligibility at the participating ENT departments. Given a signed declaration of consent patients will be enrolled and randomized in the study to either the standard cold steel tonsillectomy or to IDTS tonsillectomy.

After surgery all patients will be brought to the recovery room for 1-4 hours or hospitalized for a day. Before hospital discharge a surgeon will check for postoperative hemorrhaging and the patient and caregivers will receive oral and written recommendations for the postoperative period. Patients or caregivers are requested to follow the recommendations, and they are instructed to contact the ENT department or to call an ambulance, if postoperative hemorrhage occurs.

There will be no planned postoperative visits at the hospital. During the first six postoperative months included patients/caregivers are asked to complete electronic questionnaires online on their mobile device: daily, for the first two postoperative weeks, and again one month and six months postoperatively.

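### The blood-loss rule subtracts the dry gauze but names no post-operative weight for the used gauze, so as written it does not give total blood loss

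*Protocol*

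**What the plan says.** The protocol's Outcome Assessment section places blood loss among the primary endpoints: "Intraoperative blood loss assessed by a standardized protocol utilizing the gravimetric method". The steps follow in order.

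- Before or during surgery: "The nurse suctions up 100 ml of NaCl weighed on the scale for precision", and "The suction canister is also weighed on the scale, as well as the dry gauze".
- After surgery: "the canister of blood including the NaCl is weighed and the dry weights of the canister and gauze including the NaCl are subtracted".
- Claimed result: "this leaves the total blood loss of the operation".
- Conversion: "It is assumed that 1 gram blood = 1 ml blood".

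For scale, the Introduction cites preliminary results with the IDTS device, among them "a reduced intraoperative blood loss to 1-10 milliliters". The protocol gives no gauze weight, no number of gauzes and no gauze use by arm.

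**The concern.** A gravimetric balance is right only if everything deducted as a dry weight is also present in the gross weight. Here the canister and the NaCl appear on both sides. The gauze appears only on the side that is deducted. Two things follow if the steps are carried out as printed: the blood held in the gauze is not counted, and the weight of the gauze itself is taken off blood that was suctioned.

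At stake is whether a listed primary endpoint measures what it is said to measure. The volumes cited for the device are small, so an error of a few grams matters. The measurement is also made by theatre nurses at several departments. A team that follows the text and a team that adds the used gauze on its own initiative would enter different quantities under one variable name.

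**Working it through.** The protocol states no worked figure for this rule, so the check is a mass balance.

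**Inputs from Outcome Assessment:** C = empty canister, N = NaCl, G = dry gauze, and 1 g taken as 1 ml. Let S be blood suctioned into the canister and A blood absorbed in the gauze. True loss is T = S + A.

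**Rule as written**

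- Gross weight after surgery: C + N + S
- Deducted: C + G + N
- Result: (C + N + S) − (C + G + N) = S − G
- Error: (S − G) − (S + A) = −(G + A)

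The error is never positive, and the result is negative whenever G > S.

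**Rule with the used gauze in the gross weight**

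- (C + N + S + G + A) − (C + G + N) = S + A = T

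The error is then zero for any gauze weight.

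**Size under assumptions.** The protocol gives neither G nor the absorbed share. I assume G = 2 to 20 g and 0 to 50% of the blood absorbed. Recorded value = T × (1 − share absorbed) − G:

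| True loss (ml) | Dry gauze (g) | Recorded, 0% absorbed (ml) | Recorded, 50% absorbed (ml) |
|---|---|---|---|
| 1 | 2 | −1.0 | −1.5 |
| 5 | 2 | 3.0 | 0.5 |
| 5 | 5 | 0.0 | −2.5 |
| 5 | 10 | −5.0 | −7.5 |
| 10 | 2 | 8.0 | 3.0 |
| 10 | 5 | 5.0 | 0.0 |
| 10 | 10 | 0.0 | −5.0 |
| 10 | 20 | −10.0 | −15.0 |
| 30 | 5 | 25.0 | 10.0 |

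At the light end (2 g) the reading stays positive for a true loss of 5 or 10 ml but is still too low. From about 5 g upward the error can equal or exceed the loss being measured on the 1-10 ml scale.

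**Between arms.** The Statistical analysis section evaluates endpoints as group differences. Under the literal rule,

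recorded mean difference = true mean difference − [mean(G + A) in IDTS − mean(G + A) in cold steel].

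The bracket is zero only if mean dry gauze plus absorbed blood is the same in both arms. For illustration, take a true loss of 10 ml in both arms and 25% absorbed, so S = 7.5 ml:

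- G of 5 g versus 5 g: 2.5 − 2.5 = 0 ml.
- G of 5 g versus 10 g: 2.5 − (−2.5) = 5 ml, spurious.
- G of 5 g versus 15 g: 2.5 − (−7.5) = 10 ml, spurious.

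These pairs are invented to show sensitivity. Nothing in the protocol says which of them applies.

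**Between centers.** For one patient with T = 10 ml, G = 5 g and 25% absorbed, a team following the text records 2.5 ml. A team that also weighs the used gauze records 10 ml. The gap is 7.5 ml for the same operation.

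**The case against.** The strongest reply is that this is a drafting slip and not a faulty measurement. The method is called gravimetric and standardized, the dry gauze is weighed beforehand, and the result is described as the total. Deducting dry gauze makes sense only if the used gauze is in the gross weight. Negative readings would also be noticed by whoever does the weighing. The front matter lists a table of measurements and definitions whose body could not be read here, and it or the standardized procedure may contain the missing step.

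Most of this stands. An omitted step in the wording is at least as likely as a real mis-measurement, and a reader who infers that the recorded data are biased low goes further than the document allows. It does not rescue the sentence: the steps as printed do not give the result claimed for them, and no other text that could be read supplies the used gauze.

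A reader might also infer that the error favors one arm because the techniques differ. The protocol does not support that. It gives no gauze use by arm, and the Introduction mentions ligation or electrocautery for cold steel, not packing. Neither equality nor inequality is established.

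The 1-10 ml figure is a preliminary result from a cited pilot study and not a planning value of this trial. It serves only as a yardstick.

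**Conclusion.** The rule is wrong as written. Taken literally it yields suctioned blood minus dry gauze weight, with error −(dry gauze + absorbed blood). Under the assumed 2 to 20 g of gauze and up to half of the blood absorbed, the reading for a true loss of 10 ml is 2 to 25 ml too low. If the used gauze is in fact weighed, or placed in the canister, the error is zero. The protocol does not settle which is done, so the finding concerns the stated rule and not data already recorded. The direction and size of any between-arm distortion cannot be determined.

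The reach is limited. Blood loss is listed as a primary endpoint, but the Primary objective names hemorrhage and pain, and the sample size rests on hemorrhage. The non-inferiority conclusion on hemorrhage does not depend on this measure.

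A reader might add that enrolling "All elective and acute patients referred to tonsillectomy, with or without adenoidectomy" calls for adenoidectomy as a covariate for blood loss. That does not follow from this defect. Randomization balances adenoidectomy in expectation, so it is a separate question of precision.

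**What to change.** Replace the subtraction sentence with an explicit rule:

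blood loss (g) = [canister with contents + all used gauze, weighed after surgery] − [empty canister + NaCl + dry weight of the same gauze].

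Ask each site to confirm in writing how it has been measuring, in particular whether the used gauze was weighed or placed in the canister. If practice already matches this rule, only the wording changes. If it differs between sites, record which rule each site used, so that the values are not pooled as one quantity without comment.

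The cost is one sentence of protocol text, a query to the sites and, where it is not yet done, one extra weighing on the scale already specified.

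### Operative time and blood loss, two primary endpoints, are measured over the whole session, so a concurrent adenoidectomy adds variation unrelated to tonsillectomy technique

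*Protocol*

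**What the plan says.** Under Method (Course), the protocol states: "All elective and acute patients referred to tonsillectomy, with or without adenoidectomy, on benign indications will be assessed for eligibility". None of the exclusion criteria removes combined procedures.

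Under Outcome Assessment, intraoperative blood loss and operative time are both listed as primary endpoints. Time is "Operative time in minutes from the Boyle-Davis gag is placed until it is removed", recorded by the operating nurse. Blood is obtained by weighing canister and gauze after surgery and subtracting the dry weights and the saline; "this leaves the total blood loss of the operation". The section does not say what happens to the clock or the canister when an adenoidectomy is also done.

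The Introduction describes the two techniques under comparison as ways of working in one anatomical space: "In cold steel tonsillectomy the peritonsillar space is dissected with metal instruments", and "With the IDTS the peritonsillar space is dissected and sealed in one step". It reports pilot results with the tissue sealer (IDTS) of "a shortened operative time with a median time of 5.1 minutes (range 1.5-26.5 minutes), and a reduced intraoperative blood loss to 1-10 milliliters".

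Under Method (Design), randomization is blocked by department. Under Statistical analysis, continuous data are compared with a t-test or a Mann-Whitney test. The listed confounders do not include adenoidectomy, and the model named for them is logistic.

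**The concern.** The trial asks about tonsillectomy technique, but in combined procedures these two endpoints can also measure a second procedure that is not part of the comparison. The values being measured are small. The cited pilot levels with IDTS are a median of 5.1 minutes and 1 to 10 ml, so a few added minutes or millilitres can be a large part of one patient's recorded value.

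Four things are at stake: precision; the size of any effect expressed as ranks or percentages; exposure to chance imbalance in the number of combined procedures per arm; and the meaning of the reported medians, which will move with case mix. A statistical analysis plan could adjust for adenoidectomy or form subgroups. It could not reconstruct a patient's tonsillectomy-only time or blood loss if the two parts were never recorded separately.

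**Working it through.** **The plan's own figure.** The only sample-size calculation is for post-tonsillectomy hemorrhage (Power Considerations: 7.9%, limit 4%, power 80%, level 0.05). Taking the level as one-sided, n per arm = 2 × 0.079 × 0.921 × (1.645 + 0.842)² / 0.04² ≈ 562.3, rounded up to 563, or 1126 in total. This reproduces the stated 1126 and does not involve time or blood loss. The 563 per arm is used below.

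**Inputs that must be assumed.** The protocol gives no share of combined procedures (q), no mean (m) or SD (a) of added adenoidectomy time, no SD of tonsillectomy time (s), and no cold-steel values.

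**Absolute mean difference.** An addition with the same distribution in both arms adds q × m to each mean, which cancels in the difference. The expected bias is zero.

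**Variance.** Inflation = [s² + q·a² + q(1−q)·m²] / s². With q = 0.30, m = 5, a = 3, the added term is 0.3 × 9 + 0.21 × 25 = 2.70 + 5.25 = 7.95.

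| s (min) | Inflation | Effective sample (1/inflation) |
|---|---|---|
| 4 | 23.95/16 = 1.50 | 67% |
| 6 | 43.95/36 = 1.22 | 82% |
| 8 | 71.95/64 = 1.12 | 89% |

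Extremes over q = 0.15 to 0.50, m = 3 to 8, a = 2 to 4, s = 4 to 8:
- Worst: (16 + 8 + 16)/16 = 2.5, effective sample 40%.
- Best: (64 + 0.60 + 1.15)/64 = 1.03, effective sample 97%.

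**Chance imbalance.** The SE of the shift in mean time is m × √(2q(1−q)/563). For q = 0.30 and m = 5 it is 5 × √(0.42/563) = 0.14 min. It runs from 0.09 to 0.30 min over q = 0.1 to 0.5 and m = 5 to 10.

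**Rank effect.** With log-normal times (log-SD 0.6, median 5.1 min for IDTS and an assumed 10 min for cold steel), the probability that an IDTS case is shorter is Φ(ln(10/5.1)/(0.6√2)) = 0.79. In simulation it falls to 0.75 with 30% combined and 5 min added, and lies between 0.78 and 0.71 over 15% to 50% combined and 3 to 8 min added.

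**Relative effect.** With the same 5.1 and 10 min, the ratio 0.51 becomes (5.1 + 1.5)/(10 + 1.5) = 0.57 at q = 0.30, m = 5. For blood, an assumed 15 ml in 30% of patients adds 4.5 ml per arm. An assumed 5 versus 25 ml (80% less) becomes 9.5 versus 29.5 ml (68% less), while the difference stays at 20 ml.

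**Case mix.** With m = 5, mean session time rises by 0.75 min at q = 0.15 and by 2.5 min at q = 0.50, with no change in technique.

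**The case against.** The strongest reply is that randomization protects the comparison. The Statistical analysis section plans to evaluate differences between groups, and an equal addition leaves the expected mean difference intact. That stands. A reader might infer bias for or against IDTS, and the documents do not support it.

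Second, the lost precision may not matter. If the true difference were 7 minutes, then even at 40% effective sample (about 225 of 563 per arm) and s = 4, the SE is 4 × √(2/225) = 0.38 min and z is about 18; at s = 8 it is about 9. This also stands for a large difference. For a small one it does not: with an assumed true difference of 1 minute and s = 6, power falls from 80% to 73% if adenoidectomy adds 5 min (SD 2) in 30% of patients. The protocol supports neither difference.

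Third, some tempting statements go beyond the text. The 5.1 minutes and 1 to 10 ml are levels seen with IDTS, not gains over cold steel. That adenoidectomy falls within the gag interval, or is done with neither study technique, is a plausible inference from the Introduction but is not stated. One also cannot assert that separate values are unavailable. The tables of measurements and register data are not shown, and the database holds peroperative information.

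Finally, session time and total blood loss are legitimate, objective outcomes, and the stated primary objective names hemorrhage and pain. True, but the protocol itself lists both as primary endpoints, and the Discussion includes surgery time in its hypothesis.

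**Conclusion.** The point holds as a weakness in how two primary endpoints are defined. It is neither a contradiction nor a source of systematic bias. For blood loss the wording plainly takes in the whole operation. For time, adenoidectomy is counted if it is done with the gag in place, which the protocol leaves open.

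The consequence is extra variance, diluted rank and relative effects, room for chance imbalance, and medians that depend on the share of combined procedures. Under the central assumptions above, the variance of operative time rises by 12% to 50%; over the wider range, the effective sample is 40% to 97%. Every one of these figures rests on assumed inputs, and the range runs from serious to negligible. The calculation for hemorrhage is untouched. The case for acting is that the remedy costs very little.

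**What to change.** - **Outcome Assessment:** define operative time for the tonsillectomy part. The operating nurse notes the start and end of any adenoidectomy, and that interval is subtracted where it falls between gag placement and removal. Keep the session total as a secondary value.
- **Statistical analysis:** stratify or adjust the time and blood-loss comparisons by concurrent adenoidectomy (yes/no), and show both endpoints for tonsillectomy-alone patients. This also covers patients whose adenoidectomy was not timed.
- **Optional, where practical:** weigh canister and gauze at the changeover, so that adenoidectomy blood is recorded separately.

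The cost is two extra time stamps in combined procedures, the database fields to hold them, and a little more analysis. The optional weighing asks more of the theatre team, which is why it should not be mandatory.

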**Table 1:** Overview of measurements, timing, and definitions.

**Table 2:** Overview of data entered in the online register by both physician and patients.

**Figure 1:** Participating ear, nose and throat departments in Jutland are: Aalborg University Hospital and Thisted Hospital. Gødstrup Hospital. Esbjerg Hospital. Lillebælt Hospital, Vejle. Sønderjyllands Hospital, Sønderborg.

**Figure 2:** Eligible patients who have signed a written consent are included in the study. Patient information is entered into the tonsil database by the surgeon. The computer randomly assigns patients to two study arms via block randomization. The control group undergoes standard cold steel tonsillectomy. The investigational group receives tonsillectomy with impedance dependent tissue sealer device. The per-operative procedure is equal for both groups as well as postoperative recommendations. The patients or their caregivers answer daily questionnaires on their mobile device regarding adherence to postoperative recommendations; pain scores on a Likert scale for adults/Wong-Baker scale for children; activity level; food consumption; unscheduled contacts to the health care system; return to school, work or childcare; satisfaction with the procedure; health related quality of life on the EQ5D-SL questionnaire; and quality of taste and smell. If post-tonsillectomy hemorrhage, infection, rehospitalization for rehydration occurs the doctor will input a detailed account in the database.

**Randomized controlled trial on Cold Steel versus Impedance Dependent Tissue Sealer tonsillectomy comparing postoperative morbidity**

Authors: [name]^1^; [name]^1^; [name]^3^; [name]^4^; [name]^5^; [name]^6^; [name]^1,2^.

Affiliations: 1 University Clinic for Balance, Flavour and Sleep, ENT department Gødstrup, [name], 2 Department of Clinical Medicine, Aarhus University, [name], 3 Ear, nose and throat department, Aalborg University Hospital, [name]; 4 Ear, nose and throat department, Sygehus Sønderjylland, [name], 5 Ear, nose and throat department, Sygehus Lillebælt, [name], 6 Ear, nose and throat department, Sydvestjysk Sygehus, [name].

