**Primary objective**

The aim of the study is to evaluate whether tonsillectomy performed with an IDTS is non-inferior compared to tonsillectomy performed with cold steel instruments in terms of PTH and postoperative pain.

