**Statistical analysis**

Endpoints will be evaluated as differences between treatment groups. Categorical data are analyzed by chi2 or Fisher’s exact test. Depending on normal distribution, continuous data is analyzed by either un-paired Student’s *t-test* or Mann-Whitney rank sum test. An Intention-to-treat principle will be used including all randomized participants in the analysis. Stratification will be performed, and confounding factors (sex, age, surgical indication, BMI, smoking, comorbidity) analyzed in a multiple logistic regression model. Repeated measurement data will be analyzed in a mixed effect model for repeated measurements (ANOVA) with group and time as systematic factors and patients as random effect. The model takes random variations over time into account. Post-hoc tests will be based on the Kenward-Roger approximation to test all included patients despite missing data. The significance level is set at 0.05.

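### The primary pain endpoint uses one scale for adults and another for children, names the adult scale two ways, and on a plain reading is analysed in one model without a term for the scale

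*Protocol*

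**What the plan says.** The Protocol's Primary objective is to show that the tissue sealer is "non-inferior compared to tonsillectomy performed with cold steel instruments in terms of PTH and postoperative pain". Outcome Assessment accordingly lists pain among the primary endpoints.

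The measurement is described in two places:

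- Outcome Assessment: "Postoperative pain is assessed on an 11-point numeric rating scale", running from 0 to 10 with both ends labelled, and then "For children, the Wong-Baker Faces rating scale will be used".
- Figure 2 legend: "pain scores on a Likert scale for adults/Wong-Baker scale for children". The same legend has patients or their caregivers answering the daily questionnaires.

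For data collected repeatedly, Statistical analysis names a "mixed effect model for repeated measurements (ANOVA) with group and time as systematic factors and patients as random effect". It adds that the post-hoc tests use the Kenward-Roger approximation "to test all included patients despite missing data". Age appears once in that section: "Stratification will be performed, and confounding factors (sex, age, surgical indication, BMI, smoking, comorbidity) analyzed in a multiple logistic regression model". Neither the scale used nor an age group is named as a factor for the pain scores.

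**The concern.** There are two linked problems.

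First, a primary endpoint should have one definition. The adult scale is a 0-to-10 numeric rating in one place and a Likert scale in another, and the protocol does not say that these are the same thing.

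Second, child and adult scores come from different instruments, and for some patients a caregiver answers. Suppose all scores enter one model with only treatment group, time and patient. Any systematic difference in level between the scales then goes into the between-patient variance, and any difference in recovery curve goes into the residual. The treatment contrast is made between patients, so it loses precision. The estimated difference is also an average over points on two scales. One point of that average has no single clinical meaning, which matters when the stated aim is to conclude non-inferiority on pain.

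**Working it through.** **Is pooling what the plan says?** Four statements, set side by side:

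1. Pain is collected daily for two weeks, then at one and six months (Method, Course). It is therefore repeated measurement data.
2. The only model given for such data has group, time and patient.
3. The testing is meant to cover all included patients, children and adults alike.
4. Age is assigned to a logistic regression, which is for a binary outcome such as hemorrhage.

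One pooled model without a scale term is the plain reading, although the text does not say it outright. The t-test and Mann-Whitney test named for continuous data have no place for such a term either.

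**The plan's own figure.** The protocol has no calculation for pain. Its sample size concerns hemorrhage only and supplies the number per arm used below. With 7.9% in both arms, a 4% limit, one-sided 0.05 and 80% power:

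n = 2 × 0.079 × 0.921 × (1.645 + 0.842)² / 0.04² ≈ 562.3, so 563 per arm and 1126 in total, as stated.

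**Assumed inputs, not in the protocol:** SD within a scale of 2.5 points (variance 6.25); share of children f = 0.3 or 0.5; difference in mean level between the scales on a given day δ = 1, 2 or 3 points.

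**Formulas.** Extra variance from omitting the scale term = f(1 − f)δ². Share of total = extra / (6.25 + extra). 95% half-width of the treatment difference on one day = 1.96 × SD × √(2/563).

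| δ | Extra variance, f = 0.3 / 0.5 | Share of total, f = 0.3 / 0.5 | SD at f = 0.5 | Half-width at f = 0.5 |
|---|---|---|---|---|
| 1 | 0.21 / 0.25 | 3% / 4% | 2.55 | 0.298 |
| 2 | 0.84 / 1.00 | 12% / 14% | 2.69 | 0.314 |
| 3 | 1.89 / 2.25 | 23% / 26% | 2.92 | 0.341 |

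With the scale term in the model the half-width is 1.96 × 2.5 × √(2/563) = 0.292. The loss is therefore under 0.01 points at δ = 1 and about 0.05 points at δ = 3.

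A second set of assumptions (20% to 50% children, level difference of 0.25 to 1.0 SD) inflates the variance by a factor of 1.01 to 1.25, an effective sample loss of 1% to 20%.

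These are single-day figures. The precision of a difference averaged over days also depends on the split between within-patient and between-patient variance, which the protocol does not give.

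**Bias.** Which scale a patient gets depends on being a child or an adult, which is fixed before treatment and independent of the allocated arm. The expected treatment difference is therefore unaffected. Chance imbalance in the share of children has SD √(2f(1 − f)/563), which is 0.030 at f = 0.5. Multiplied by a level difference of 1 SD, it shifts the treatment difference by an SD of 0.030 SD units.

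**Interpretation.** As a constructed example, let the arms differ by 1 point in adults and 0 in children, with equal shares. The pooled estimate is 0.5 × 1 + 0.5 × 0 = 0.5, a value that applies to neither group.

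**The case against.** The strongest reply is that pooling is inferred. Statistical analysis does not mention pain by name, and it announces stratification in the same sentence that lists age. A statistical analysis plan, not available here, could add covariates; group, time and patient form a valid core model that excludes nothing. This stands in part. However, the stratification names no factor and no endpoint, and age is tied to a model that cannot serve pain scores. As written, the protocol points to a pooled analysis.

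It can also be said that "Likert" is loose naming of the 0-to-10 scale in a figure legend. That may well be so. The legend gives no categories, so the documents do not show that a different adult instrument is in use. They show only that the two places disagree.

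The size is modest and every input is assumed. This stands in full.

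A reader might infer three stronger things that the documents do not support:

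- *The comparison of techniques is biased.* Randomization rules this out, as shown above.
- *Departments may give the same adolescent different scales.* Patients and caregivers complete electronic questionnaires on their own devices, and nothing gives departments a choice of scale.
- *No age separates the two scales.* Tables 1 and 2, which cover definitions and the data entered, are listed but their content is not shown. An age limit may be there.

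Finally, a scale term and a scale-by-time term would not by themselves reveal a treatment effect that differs between children and adults. That needs the treatment difference within each scale.

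**Conclusion.** The point holds as a moderate improvement to a primary endpoint. The two names for the adult scale are an inconsistency in the protocol and need reconciling. The pain model, read plainly, leaves out a factor that the trial already knows for each patient. The consequence is some loss of precision and a pooled difference that is hard to interpret. It does not invalidate the randomized comparison.

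The size rests on assumptions: SD 2.5, 30% to 50% children, a level difference of 1 to 3 points and 563 patients per arm. Under these the loss is about 3% to 26% of single-day variance, and at worst a half-width of about 0.34 instead of 0.29 points. If the two scales yield similar levels in practice, the precision loss is negligible and only the questions of naming and interpretation remain.

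**What to change.** 1. Use the same name for the adult scale in the Figure 2 legend and in Outcome Assessment.
2. In Statistical analysis, add scale (adult numeric or child faces) and scale-by-time as fixed effects in the repeated-measures model for pain. The scale term will also carry the average difference between children and adults; for this purpose the two need not be separated.
3. Report the treatment difference within each scale, from a group-by-scale term, beside the combined estimate.

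The cost is a few lines of text, the added model terms and a little more reporting. Sample size, allocation and data collection schedule do not change.

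The downside is lower precision of the separate estimates. With SD 2.5 and 563 per arm, the single-day half-width within one scale is 1.96 × 2.5 × √(2/281.5) ≈ 0.41 points at equal shares. With 30% children it is 1.96 × 2.5 × √(2/168.9) ≈ 0.53 for children and 1.96 × 2.5 × √(2/394.1) ≈ 0.35 for adults. The separate estimates should therefore be presented as support for reading the combined result.
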